### Participant

5.6

*Sampling and sample size:* Consecutive sampling will be used to recruit the participants. Using the statistical superiority sample size design,^[34]^ a sample of size of 36 participants per group will be sufficient to show a statistical difference in the bone mineral density between the control and the experimental group. For this study, the groups are divided into four which are the experimental group (HIV+ and HIV−) and the control group (HIV+ and HIV−), therefore, at least a total of 144 patients per study site will be recruited to participate in the study. The sample size will be calculated using Equation 1:(1)$$N=2\times \left\{Z_{1-\alpha /2}+Z_{1-\beta }/d2\right\}\times Pooled\;SD$$

where N = total sample size per group, *Z*_1−α/2_ = 1.96, *Z*_1−β_ = 0.845, *d*^2^ = 0.1 and pooled standard deviation = 0.093.

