### Allocation

5.8

Blocked allocation will be used to allocate the participants into groups. Random numbers will be generated to allocate the patients into intervention and control groups in blocks (10 numbers equally distributed into intervention and control groups). There will be two blocks namely

1.HIV-positive and2.HIV-negative blocks.

The number allocation will be done by independent research support. Opaque envelopes will be used to conceal the allocation.

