### Assessments

5.10

Baseline and follow up assessment will be conducted by a qualified physiotherapist (Research assistant) who will be blinded to the study.

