### Statistical analysis

5.15

Data to be collected shall include discrete and normally distributed continuous variables. The normal distribution of the continuous variables will be tested using the Shapiro–Wilk test, and depending on the outcome, parametric or non-parametric statistics will be used to analyze the data. The change in the categorical outcomes across the time points will be measured using the McNemar's test. The difference in the continuous outcomes between the groups will be measured using the independent *T*-test (parametric) and Mann–Whitney *U* test (non-parametric). Intention to treat analysis method will be used for this study. Alpha shall be set at *P* < .05 (two-tailed). All analyses will be intent-to-treat and missing data will be treated as missing.

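### Continuous outcomes get an unadjusted two-sample test chosen by a normality pretest, which forgoes precision from baseline, HIV strata and repeated visits and leaves the effect measure open

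*Protocol article*

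**What the plan says.** Section 5.15 (Statistical analysis) tests normality by Shapiro–Wilk and then, "depending on the outcome, parametric or non-parametric statistics will be used to analyze the data". For between-group comparisons: "The difference in the continuous outcomes between the groups will be measured using the independent" t-test in the parametric case and the Mann–Whitney U test otherwise. The error rate is given as "Alpha shall be set at *P* < .05 (two-tailed"). The only method named for change over time is McNemar's test, for categorical outcomes. The section names no covariate, stratum or repeated-measures method for continuous outcomes. It does not say whether follow-up values or changes are compared, or whether the HIV strata are pooled.

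The design offers more than these tests use:

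- Section 5.10: "Baseline and follow up assessment will be conducted", so there is a baseline.
- Section 5.12: visits at 2, 6 and 12 weeks and at 6 months after surgery. The first is the baseline and three follow.
- Section 5.8: randomisation in blocks of 10, with separate lists by HIV status ("There will be two blocks namely" HIV-positive and HIV-negative). Site is not named as a stratum.
- Sections 5.2 and 5.6: a multi-centre 1:1 trial with at least 144 patients per site, where "the groups are divided into four which are the experimental group (HIV+ and HIV−) and the control group (HIV+ and HIV"−).

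**The concern.** A two-sample test on follow-up values treats each patient as if nothing had been measured before treatment. Where an outcome correlates with its own baseline, that information narrows the interval at no cost. HIV status was considered important enough to stratify the randomisation. If the strata are then pooled without adjustment, the standard error includes between-stratum variation that the allocation has already balanced out.

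The pretest raises a different issue. Whether the result is a difference in means or a comparison of ranks depends on a p-value from the same data. The answer can differ between visits of the same outcome and depends on sample size. The Mann–Whitney test also gives no covariate-adjusted effect estimate.

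**Working it through.** **The plan's own figure.** Section 5.6 claims that "a sample of size of 36 participants per group will be sufficient", with z-values 1.96 and 0.845, a quantity of 0.1 and SD 0.093 ("0.845, *d*^2^ = 0.1 and pooled standard deviation = 0.093"). Reading 0.1 as the difference to detect, the usual formula gives 2 × (1.96 + 0.845)² × 0.093² / 0.1² = 13.6, i.e. 14 per group, so 36 is not reproduced. That is a separate matter. Below, 36 per group and SD 0.093 are taken as stated.

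**Inputs not in the document.** The baseline-to-follow-up correlation rho (range 0.3 to 0.8) and the HIV-positive versus HIV-negative difference (range 0.25 to 1 within-stratum SD) are assumptions.

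**1. Precision from baseline (36 v 36, one HIV stratum at one site).** ANCOVA multiplies the variance of a follow-up comparison by 1 − rho². The difference detectable with 80% power is (1.96 + 0.845) × 0.093 × √(2/36 × (1 − rho²)).

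| rho | variance factor | 36 per group works like | detectable difference |
|---|---|---|---|
| 0 (plain t-test) | 1.00 | 36 | 0.061 |
| 0.3 | 0.91 | 40 | 0.059 |
| 0.5 | 0.75 | 48 | 0.053 |
| 0.7 | 0.51 | 71 | 0.044 |
| 0.8 | 0.36 | 100 | 0.037 |

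An effect that the t-test detects with 80% power is detected by ANCOVA with 83.6%, 89.9%, 97.5% and 99.7% power at these four correlations.

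If change scores were intended, their variance factor is 2(1 − rho). ANCOVA's variance relative to theirs is (1 − rho²) / [2(1 − rho)] = (1 + rho)/2, which is 0.80 at rho 0.6 and 0.90 at rho 0.8. The remaining gain is then 20% to 10%. Below rho 0.5, change scores are worse than no adjustment.

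**2. Pooling the HIV strata.** With equal strata and an HIV difference of g within-stratum SDs, the pooled variance is inflated by 1 + g²/4, but the true sampling variance is not. The standard error is therefore too large by √(1 + g²/4), and the true size is 2 × [1 − Φ(1.96 × √(1 + g²/4))].

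| g | SE ratio | true size |
|---|---|---|
| 0.25 | 1.008 | 4.8% |
| 0.5 | 1.031 | 4.3% |
| 1.0 | 1.118 | 2.8% |

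A simulation of 6,000 trials per setting, with blocks of 10 within HIV strata and 36 per arm-by-HIV cell (72 v 72), agrees. The t-test's size was 5.2%, 4.1% and 2.9% at g = 0, 0.5 and 1, against 5.0%, 4.9% and 5.0% for ANCOVA with baseline and HIV stratum. With rho 0.7 and a true effect of 0.47 SD, power was 80.4%, 78.4% and 73.2% for the t-test and about 97.5% throughout for ANCOVA.

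**3. The pretest.** At 36 or 72 per group, the two-stage procedure had type I error of 0.049 to 0.050 with normal data and 0.050 to 0.054 with lognormal data. It switched to Mann–Whitney in about 10% of truly normal trials, as expected from two groups each tested at 5% (1 − 0.95² = 9.75%). For a mildly skewed gamma distribution (shape 20, skewness 2/√20 = 0.45), Shapiro–Wilk rejected in about 15% of samples at n = 36 and 48% at n = 144. The same population thus leads to different effect measures depending on n.

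**The case against.** Several objections have force.

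- **The strata may not be pooled.** Section 5.6 sizes four groups of 36, so testing within each HIV stratum is a plausible reading. It would remove the standard-error problem in step 2, but not the loss from ignoring baseline and visits. Steps 1 and 2 therefore describe two possible analyses and their figures should not be added together.
- **The trial may have power to spare.** If 0.1 is the bone mineral density difference, 36 per group with SD 0.093 already gives 99.5% power with a plain t-test. This stands for that outcome. The abstract also lists function, gait, physical activity and quality of life as primary, and no sample size is given for those.
- **The correlation is unknown.** Section 5.5 leaves the densitometer's test-retest reliability to be determined in this study. At rho 0.3 the gain is only 9%.
- **Model details belong in an analysis plan.** True of covariance structures and the like. Here, however, the article itself fixes the test and the rule for choosing it.

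A reader might also infer three stronger claims that the document does not support. First, that ignoring site distorts the standard error as ignoring HIV does. This would need allocation balanced by site, and section 5.8 names HIV strata only, so omitting site costs precision and nothing more. Second, that the unadjusted test throws away most of the attainable precision. Even on follow-up values the variance reduction is 36% at rho 0.6, and it is smaller against change scores. Third, that the pretest or the missing adjustment produces excess false positives. Step 3 shows no material inflation, and the error in step 2 is conservative.

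**Conclusion.** The point holds as one of efficiency and prespecification, not of validity. The stated tests do not use the baseline, the HIV strata or the repeated visits. Using baseline alone would reduce the variance of a follow-up comparison by 9% to 64% over the assumed correlations. If strata are pooled, the unadjusted intervals are too wide by about 3% or 12% for an assumed HIV effect of 0.5 or 1 SD, and negligibly so at 0.25 SD. The Shapiro–Wilk rule leaves the effect measure undetermined until the data are seen. The size of the loss rests on the assumed correlation and HIV effect, on a roughly equal HIV split, and on follow-up values being what is compared. The direction does not depend on the exact values. The change should be made because it costs almost nothing.

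**What to change.** In section 5.15, delete the Shapiro–Wilk switch and prespecify one ANCOVA or linear mixed model for each continuous outcome that has a baseline value. The response is the follow-up value. The terms are baseline value, arm, visit, arm-by-visit, HIV stratum and site. Report the adjusted mean difference with its 95% confidence interval at one named visit.

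Add an arm-by-HIV term, or stratum-specific estimates, for the question about adults living with HIV that the four-group sample size implies. Fit outcomes that exist only in HIV-positive patients, such as viral load, without the HIV terms. Fit outcomes with no pre-treatment value, such as exercise adherence, without the baseline term. Prespecify a log transformation for skewed markers such as CRP and viral load.

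The cost is analysis wording only. Baseline values, HIV status, site and visit are already part of the planned data, and no patient, visit or measurement is added.

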### Eligibility criteria

5.4

The study population will consist of all persons with femoral fracture and HIV-positive and negative (HIV-positive medically confirmed) aged 18 to 60 years attending the above-named health facilities. For the HIV-positive participants, a documented positive HIV result, as well as a history of being followed-up at the HIV treatment and care center.

Inclusion criteria

Only patients between 18 and 60 years at the last birthday and not more than 60 years at the next birthday.For HIV-negative participants, willingness to accept HIV testing.All patients on ART therapy with femoral shaft fracture will be recruited.All patients with lower limb fractures (femur) will be recruited.All patients must be ambulant.

Exclusion criteria

Severely ill persons based on investigator judgment.Presence of any bone or rheumatic disorder.Fracture of the femoral neck.

*Interventions*: The intervention programme will be a home-based exercise programme targeted at improving bone mineral density, function, gait, QoL, and physical activity. The intervention programme aims to improve the joint range of motion, gait training, muscle strengthening, and balance. The participants in the intervention group will be followed up weekly via phone calls to monitor the intervention and ensure adherence to the programme.

*Control group*: The control group will continue with their usual rehabilitation programme as conducted by the various clinics.

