### Main study

5.12

The research will recruit patients with femoral fracture being managed at the orthopaedic department at CHBAH, and the following process will be used as a guide for the recruitment, blinding, and allocation. The main study procedure will follow the recruitment, allocation, blinding and intervention guidelines as presented. The CONSORT diagram below in Figure 1 will be used to report the recruitment and allocation of the participants. The time of recruitment and assessment is the usual routine clinic check-up of the patients in the orthopaedic surgery department (2-weeks, 6-weeks, 12-weeks, and 6-months post-surgery).

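### All analyses are labelled intention-to-treat, but the fixed missing-data rule with the named two-sample tests gives an available-case analysis by allocated arm

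*Protocol article*

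**What the plan says.** The Statistical analysis section (5.15) of the protocol article commits to intention-to-treat twice. The first statement is "Intention to treat analysis method will be used for this study". The second extends it to everything and sets the missing-data rule in the same sentence: "All analyses will be intent-to-treat and missing data will be treated as missing".

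The section names these tests:
- Continuous outcomes between arms: "The difference in the continuous outcomes between the groups will be measured using the independent" t-test, or the Mann–Whitney U test if normality fails.
- Categorical outcomes: "The change in the categorical outcomes across the time points will be measured using the McNemar's test".

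It names no repeated-measures model, no imputation and no assumption about why data are missing.

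Two other places bear on the point. Under Main study (5.12), assessments fall at "2-weeks, 6-weeks, 12-weeks, and 6-months post-surgery". Under Interventions (within 5.4), "The participants in the intervention group will be followed up weekly via phone calls to monitor the intervention" and to support adherence. The control group paragraph describes usual rehabilitation and mentions no such calls.

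**The concern.** This is a stated rule, not a detail left for an analysis plan. An analysis plan that followed the article would inherit it. If missing values stay missing and the arms are compared by a two-sample test, every patient without the tested value leaves that comparison. A patient seen at 6 and 12 weeks but not at 6 months contributes nothing to a 6-month comparison.

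The stake is a comparison reported as intention-to-treat that does not cover all randomised patients. It may be biased if the patients who are lost differ from those who stay, and differ unequally between arms. A larger sample does not shrink that bias; it only makes a false rejection more likely.

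**Working it through.** **Step 1: what the rule and the tests imply together.** The t-test and the Mann–Whitney U test need one observed value (or change score) per analysed patient. McNemar's test needs both members of a pair. None of them uses a patient's other visits in place of an absent value. So whenever data are missing, the analysed set is smaller than the randomised set. The set can differ from test to test, which makes this available-case analysis. The article does not say which visit or change score is tested; that the tests are applied visit by visit is inferred from the four scheduled visits and the two-sample tests.

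**Step 2: when this biases the arm comparison.** Let q be the fraction lost in an arm and g the gap in mean outcome, in SD units, between those who stay and those who are lost in that arm. The observed mean exceeds the mean of all randomised patients in that arm by q × g. For arms 1 and 2:

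bias = q1 × g1 − q2 × g2.

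If g = 0 in both arms, the bias is zero however unequal the loss. If q and g are the same in both arms, it cancels. Bias therefore needs loss related to outcome within arm, and a difference between arms.

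**Step 3: illustration.** The article gives no attrition figure, so these inputs are assumptions: q1 = 0.25, q2 = 0.10, g = 0.5 to 1.0 SD in both arms, outcome SD = 1, no true effect.

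- g = 0.5: 0.25 × 0.5 − 0.10 × 0.5 = 0.075 SD
- g = 1.0: 0.25 × 1.0 − 0.10 × 1.0 = 0.15 SD

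The arm with the greater loss looks better than it is. The article does not show which arm that would be.

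**Step 4: numbers per arm.** Sampling and sample size (5.6) gives 36 per HIV-by-arm group and 144 per study site. Average loss under the assumption is (25% + 10%)/2 = 17.5%.

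- One HIV stratum at one site: 36 × 0.825 = 29.7, about 30 per arm.
- Both HIV strata and two sites: 36 × 2 × 2 = 144 per arm, and 144 × 0.825 = 118.8, about 120 per arm.

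**Step 5: rejection of a true null at two-sided 0.05.** With SE = √(2/n) and λ = bias/SE, the rejection probability is Φ(−1.96 + λ) + Φ(−1.96 − λ).

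| n per arm | SE | bias (SD) | λ | rejection |
|---|---|---|---|---|
| 30 | 0.258 | 0.075 | 0.290 | 6.0% |
| 30 | 0.258 | 0.15 | 0.581 | 8.9% |
| 120 | 0.129 | 0.075 | 0.581 | 8.9% |
| 120 | 0.129 | 0.15 | 1.162 | 21.3% |

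The unequal numbers that such loss would leave (27 against 32, and 108 against 130) change little: 6.0–8.9% and 8.9–21.0%.

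**The case against.** The strongest reply is that intention-to-treat often means only that patients are analysed in their allocated arm whatever their adherence. On that reading the sentence is coherent: patients stay in their arm and nothing is imputed. This stands in part. The narrow principle can hold for observed patients. But the article applies the label to all analyses without that qualification, and randomised patients without the tested value are not in them.

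Some stronger inferences are tempting, and the article does not support them:

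- *That the analysis is complete-case.* A patient is lost only from tests where the value is absent, so available-case is the accurate term.
- *That it is valid only if data are missing completely at random.* This is too strict. Loss that depends on arm alone, and not on outcome within arm, leaves the observed mean difference unbiased. The weekly calls bear on whether rates differ; nothing in the article shows that loss is related to outcome.
- *That every named test carries arm bias.* McNemar's test, as described, measures change over time within patients and makes no arm comparison.
- *That the loss leaves the trial short of power.* The article does not establish this. Section 5.6 prints "0.1 and pooled standard deviation = 0.093". If 0.1 is read as the difference (the notation is ambiguous), a 20% loss from 36 to about 29 per group still leaves about 98% power. The lack of a stated drop-out allowance is a separate sample-size matter.

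It is also fair to say that a mixed model corrects bias only as far as the observed data explain the loss, and that the detailed form of a sensitivity analysis may be left to the analysis plan.

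**Conclusion.** The point holds as a defect in a rule that the article itself fixes. The label promises intention-to-treat for all analyses; the rule and the named two-sample tests deliver an available-case analysis by allocated arm that ignores the other visits of patients without the tested value. Bias is plausible, given calls described for one arm only and follow-up to 6 months, but it is not demonstrated. Its size cannot be taken from the article. The 0.075–0.15 SD bias and the rejection rates of 6–9% and 9–21% rest wholly on the assumed 25% against 10% loss and the assumed 0.5–1.0 SD gap. The text should be changed, because the remedy uses visits already scheduled.

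**What to change.** For continuous outcomes, replace the sentence in Statistical analysis (5.15) with the following:

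1. Analyse all randomised patients as allocated, by a likelihood-based repeated-measures mixed model that includes baseline and every available visit. State that this is valid under missing at random.
2. Add a sensitivity analysis for data missing not at random, such as multiple imputation with a delta adjustment by arm, because the mixed model alone does not remove that bias.
3. Label any observed-case t-test or Mann–Whitney result as available-case, and not as intention-to-treat of all randomised patients.

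The cost is revised wording, modest extra programming and reliance on an assumption that is now stated. No new data or visits are needed.

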## Discussion

6

Physical exercise could influence bone metabolism and bone healing,^[52,53]^ as demonstrated in studies involving non-HIV infected individuals. There are possible translational benefits for people living with HIV. Exercise interventions may improve function, livelihood and QoL, as well as contribute to reducing hospital costs, enhancing return to work and local and national productivity. Available evidence suggests that co-morbidities associated with degeneration in HIV conditions are worsened by a lack of physical exercise and restriction in social participation leading to multi-system (neurological, musculoskeletal, cardiopulmonary, and metabolic) impairments, which are amenable to physical exercise modalities. The impact of the home-based exercise programme on bone mineral density may reduce the risk of osteoporosis. Previous studies have demonstrated this prospect but are yet to be explored in a large randomized controlled trial. As it is, most of the studies on bone disease and physical exercises in HIV condition have been done outside Africa, which by far has the highest prevalence of HIV infection globally. There are contextual, racial, and gender differences that may influence the outcomes of an exercise intervention on BMD. Such differences can alter the interventions needed, including exercise. For this reason, it is prudent to research to test the impact of an exercise intervention on BMD in HIV positive patients in an African context.

### Impact of results

6.1

The benefits of exercise interventions in HIV and HAART-related bone demineralization should be explored in a randomized controlled trial. Moreover, limitations in availability, affordability and accessibility of most HIV patients to clinics where gymnasiums are available, may limit compliance to the use and prescription of relevant exercise modalities. Therefore, we consider implementing evidence-based functional-based oriented, simplified, cost-free and innovative home-based exercises and which need to be tested for efficacy in achieving the desired therapeutic goals of improved physical functioning and BMD in HIV management. A home-based rehabilitation approach under an integrated healthcare model, which we developed in a semi-rural poor resource setting of KwaZulu–Natal, was therefore proposed as the most viable option. South Africa and Nigeria are multi-cultural societies and appear as ideal settings for such studies to enable easy recruitment of participants who are exposed to similar environmental variables that may influence bone metabolism other than genetic differences. The net effect of delayed lower limb fracture healing in HIV condition, from a population-based national outlook, suggests a substantial loss of productive manpower, decline in the overall national productivity, economic development, gross domestic product, and QoL with a predictable negative impact on the poverty level. Therefore, any interventions that could prevent/ameliorate/reverse the adverse effects of HIV and HAART-related bone demineralization should be of socio-economic significance.

